### Other study parameters (if applicable)

### To further evaluate bCBT compared to CBT-TAU, a number of explorative measures are administered.

The **BDI** (Beck Depression Inventory) (Beck et al., 1961) is a 21-question multiple choice self report inventory of the most widely used instruments for measuring the severity of depression and assesses presence and severity of depressive symptoms.

**The BSI** (Brief Symptom Inventory) (Derogatis and Melisaratos, 1983)is a 53-item, self-report symptom inventory designed to evaluate general psychopathology. It is a brief form of the SCL-90 and is designed to provide a multidimensional symptom measurement in about 10 minutes.

**PDSS** (Panic Disorder Severity Scale (PDSS) (Shear et al., 1997) is one tool that can be used to assess the severity of panic attacks. The scale is fairly simple. There are 7 questions, each one with 5 answers that are scored 0 to 4. That leads to 28 total points possible with this scale. Ascore over 9 is considered important enough to be of clinical significance..

**LSAS** (Liebowitz Social Anxiety Scale) originally developed by Liebowitz (1987) is a short questionnaire to assess the range of social interaction and performance situations feared by a patient in order to assist in the diagnosis of social anxiety disorder. The scale features 24 items, 13 relating to performance anxiety and 11 concerning social situations and has been validated as a self-report scale (Rytwinski et al., 2009)

The **PSWQ** (Penn State Worry Questionnaire) (Meyer et al., 1990)is a self-report measure to assess pathological worry in GAD patients. By adding up the value (five-point scale, range 1–5) of all 16 items (e.g., “I’m always worrying about something“); leading to a total score from 16 to 80.

The **(WSAS)** Work and Social Adjustment Scale (Mundt et al., 2002)is a 5-item patient self-report measure, which assesses the impact of a person’s mental health difficulties on their ability to function in terms of work, home management, social leisure, private leisure and personal or family relationships. The WSAS is used for all patients with depression or anxiety as well as phobic disorders.

The five item version of **The Pearlin Mastery Scale** (Pearlin and Schooler, 1978) is administered at each assessment moment (T0-T3) to assess changes in *locus of control*. Locus of control could potentially mediate treatment effect and facilitate relapse prevention. The questionnaire consists of five questions, which are scored on a five-point Likert-scale, ranging from 1 (*totally disagree*) to 5 (*totally agree*). The total score ranges from 5 to 30, with higher scores being indicative of a higher level of experienced control.

The 12-item version of **the Work Alliance Inventory** (WAV-12; (Andrusyna et al., 2001) is used to let patients rate the *quality of the work alliance* between patient and therapist at T1 (week 10). The questionnaire is administered to investigate whether the blended treatment for has an effect on the quality of the work alliance.

The questionnaire consists of 12 items, which are scored on a five-point Likert-scale, ranging from 1 (seldom or never) to 5 (always). The raw scores range from 12 to 60, with higher scores being indicative of a better alliance between therapist and patient.

**Demographic characteristics** such as age, sex, education, employment and marital status will be collected with a general demographic questionnaire. Additional questions are asked concerning **clinical anxiety characteristics** such as age of onset, number of months depressed in past 4 years, duration of current episode, medical illnesses and treatment status. In addition, patients indicate their **treatment preference** (BCBT / CBT-TAU). Finally, participants are asked about their **computer use**: number of hours spent behind a computer and reasons for use.

#### Patient evaluations

**The Client Satisfaction Questionnaire-8** (CSQ-8; (Larsen et al., 1979) will be administered at week 30 (T3). The CSQ consists of 8 questions with item-specific response categories. The total score ranges from 8 to 32, with higher scores being indicative of higher *levels of client satisfaction*.

#### The System Usability Scale (SUS, Brooke, 1996) will be administered at week 20 amongst the participants randomized to the bCBT group. The SUS consists of 10 questions with 5 response options, ranging from 0 (strongly disagree) to 4 (strongly agree). The total scores are converted to a scale ranging from 0 to 100. Higher scores are indicative of higher *usability of the online platform* that is used for the Internet sessions in the blended therapy.

#### Process data

Data for process analyses are obtained from the administration of the participating mental health care institutions and through usage statistics of the online platform. We will consider the following aspects:

**Recruitment**: how much time is required for the recruitment of patients?

**Treatment adherence**: What is the percentage of dropout during therapy, when do patients drop out (number of completed sessions)? What is the reason for treatment dropout? Number of face-to-face contacts and number of cancellations. Do patients complete homework exercises?

**Time investment**: By both the patient and the therapist.

**Table 1: Overview of measurements for anxiety.**

| **Questionnaire** | **Baseline**  **Start treatment**  **(T0)** | **Week 6-10**  **Mid-treatment**  **(T1)** | **Week 12-20**  **End treatment**  **(T2)** | **Week 64-72**  **Follow-uptreatment**  **(T3)** |
| --- | --- | --- | --- | --- |
| **Primary outcomes** |  |  |  |  |
| BAI (anxiety severity) | x | x | x | x |
| SCID-I full diagnostic interview | x |  |  | x |
| EQ-5D (general well-being) | x | x | x | x |
| SF-36 (health-related quality of life) | x | x | x | x |
| TiC-P (health-care utilization) | x | x | x | x |
|  |  |  |  |  |
| **Secondary outcomes** |  |  |  |  |
| PDDS (panic disorder, if applicable) | x | x | x | x |
| LSAS (social anxiety, if applicable) | x | x | x | x |
| PSWQ (Generalized Anxiety Disorder, if applicable) | x | x | x | x |
| BDI (depression) | x | x | x | x |
| WSAS (work and social adjustment) | x | x | x | x |
| BSI (general psychopathology) | x | x | x | x |
| CSQ (satisfaction)  Mastery Scale (locus of control)  WAI (therapeutic alliance)  SUS (system usability, bCBT only) | x | x  x | x  x | x  x |

## Randomisation, blinding and treatment allocation

Participants will be randomly assigned to either bCBT or CBT-TAU by an independent researcher, on the basis of a computer-generated block randomization table. Group allocation cannot be blinded to patients and therapists. However, outcome assessors (i.e., those conducting the SCID-I diagnostic interviews at T0 to T3) will be blinded to the allocation, in accordance to the CONSORT guidelines (Moher et al., 2010; Schulz et al., 2012).

## Study procedures

Patients will be recruited within outpatient Anxiety Disorder departments of the participating Mental Health Care site(s) of GGZingeest, GGZ Altrecht and GGZ Oost-Brabant in the Netherlands. During their intake interview, all new patients indicate whether they are willing to participate in a study. All patients with a primary diagnosis of a severe anxiety disorder (panic disorder with or without agoraphobia, social phobia, and generalized anxiety disorder) who are willing to participate will be approached by the researchers by telephone and asked to participate in the study. Participants then receive a letter containing information on the study and the informed consent form (including a return envelope).

After a week, the researchers will contact the patient again. When the patient is willing to participate, a trained researcher then screens the patients with respect to the inclusion and exclusion criteria based on the SCID-I diagnosis and the patient’s demographic characteristics, such as age.

Patients who are not eligible to participate will be notified and remitted to regular treatment trajectories within the participating specialized mental health care center(s).

If patients are eligible to participate, written informed consent will be obtained. Subsequently, patients receive an email containing an invitation to fill in the online questionnaires. When the baseline measures are completed, patients are randomized to either bCBT or CBT-TAU. Treatment duration is 12-20 weeks in the bCBT group and 12-20 weeks in the CBT-TAU group. When necessary, additional treatments are allowed for all patients at any point of time during the study.

After 6-10, 12-20 and after 64-72 weeks (52 weeks follow-up), the patient is asked to complete a number of measures (see Table 1), which consist of a diagnostic interview (SCID-I and a set of online questionnaires).

At week 64-72 (52 weeks follow-up) the full SCID-I interview is administered to assess whether the anxiety disorder is present and to determine co-morbid disorders. The SCID-I can be administered via the telephone and face-to-face at a the mental health care location, depending on patient preference. A full SCID-I interview takes 60 minutes at most. Administering sections on anxiety disorders takes about 10 minutes.
The self-report questionnaires are administered online. Patients receive an email with a personal link to their questionnaires and have one week to fill them in. The questionnaires take 30 to 45 minutes to complete.
If the measurements that are administered in the study (during and after treatment) indicate signs of relapse or suicidal ideation, the investigator will contact the therapist immediately.

## Withdrawal of individual subjects

Subjects can leave the study at any time for any reason if they wish to do so without any consequences. The investigator can decide to withdraw a subject from the study for urgent medical reasons.

### Specific criteria or withdrawal (if applicable)

### Patients are informed that participation in the study is voluntary and they have the right to withdraw consent or discontinue participation at any time, with or without stating a reason for withdrawal. Because it is not always recommended to end treatment abruptly, the patient is advised to discuss ending treatment with his or her therapist first. The decision to end study participation will not have negative effects on the further treatment, the care, and the attention each patient has a right to within GGZ Altrecht,GGZ ingest and GGZ Oost-Brabant

## Replacement of individual subjects after withdrawal

Not applicable.

## Follow-up of subjects withdrawn from treatment

Participants who decide to withdraw from treatment are asked to provide the reason for withdrawal and to fill in the post-test measurement. Participants will not be pressured or forced to comply with this request.

## Premature termination of the study

## Not applicable.

# SAFETY REPORTING

## Section 10 WMO event

In accordance to section 10, subsection 1, of the WMO, the investigator will inform the subjects and the reviewing accredited METC if anything occurs, on the basis of which it appears that the disadvantages of participation may be significantly greater than was foreseen in the research proposal. The study will be suspended pending further review by the accredited METC, except insofar as suspension would jeopardize the subjects’ health. The investigator will take care that all subjects are kept informed.

## AEs, SAEs and SUSARs

### Adverse events (AEs)

Adverse events are defined as any undesirable experience occurring to a subject during the study, whether or not considered related to [the investigational product / the experimental intervention]. All adverse events reported spontaneously by the subject or observed by the investiga­tor or his staff will be recorded.

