**SUMMARY**

**Rationale:** Anxiety disorders are highly prevalent disorders. They cause considerable human suffering and substantial societal and economic costs, estimated to be more than 1 billion euros annually. A possible way to make treatment more cost-effective lies in *blended care*. This type of treatment combines elements of both online and face-to-face cognitive behavioral therapy (CBT).

**Objective**: In this RCT, we will examine the health care efficiency of blended care treatment for patients with a severe anxiety disorder in outpatient specialized (secondary) mental health care. The results of this cost-effectiveness study will provide 1) an insight into the health-economical outcomes of ‘blended treatment’ 2) an indication whether blended treatment will add value when it is implemented in routine specialized mental healthcare settings, and 3) a good indication whether blended treatment for severe anxiety disorders in routine practice is advisable and feasible from the perspective of different stakeholders including patients, mental health service providers and health insurers.

**Study design:** A randomized controlled trial with two parallel conditions in which blended CBT will be compared to face tot face CBT treatment as usual (CBT-TAU), for anxiety disorders

**Study population:** Patients (≥18 years old) with a diagnosis of a severe anxiety disorder (panic disorder with or without agoraphobia, social phobia, and generalized anxiety disorder) who were referred to outpatient specialized mental health care services.

**Intervention**: The blended treatment consists of 12 to 20 CBT sessions, alternating between 6 to 10 face-to-face and 6 to 10 Internet sessions. Treatment as usual will consist of 12 to 20 face-to-face CBT sessions on average (CBT-TAU). (The number of sessions depends on the type of anxiety treatment).

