**Main study parameters/endpoints:** The health-economic analyses combine clinical outcomes with cost estimates. Primary clinical outcomes are 1) recovery from*,* 2) changes in anxiety symptom severity, 3) quality-adjusted life years (QALY’s), and 4) health-related quality of life. Cost estimates are 1) costs of offering the treatments and 2) patients’ out-of-pocket costs (non-medical), such as the costs of travelling to the health services and the patients’ time costs of travelling, waiting and receiving treatment. Furthermore cost estimates include 3) costs stemming from health care uptake, including costs of medication and 4) costs stemming from productivity losses due to absenteeism and reduced efficiency while at work (presenteeism).

**Nature and extent of the burden and risks associated with participation, benefit and group relatedness:** Blended treatment is not considered to add risks to the treatment, compared to treatment as usual. The questionnaires can be considered a slight burden for patients in both conditions.

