### CBT as usual (CBTAU)

In the CBT-TAU condition, patients receive on average 20 45-minutes sessions of face-to-face CBT, spread out over 12-20 weeks (depending on the type of anxiety disorder).

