**Blended CBT (bCBT)**

In the bCBT group, patients receive 6-10 face-to-face sessions and 6-10 internet sessions, which will be delivered over a period of 12-20 weeks. Treatment starts and ends with a face-to-face session. The online sessions are delivered through a secured web-based online treatment platform (Minddistrict; www.minddistrict.com). Patients access this platform with a personalized login. The website offers information that repeats and extends the contents of the face-to-face sessions. In addition, patients use the website to complete homework exercises, such as monitoring their activities, feelings, thoughts and behavior. The first online session focuses on working with the online platform. The therapist monitors patients’ online progress and provides weekly feedback prior to the next face-to-face session. Face-to-face sessions will be audio-recorded and checked, following the same procedures as in the CBT-TAU condition. Online sessions are recorded in the online treatment platform database. On completion of treatment, patients can still access the online treatment platform to re-read information and look up homework exercises, such as the relapse prevention plan.

The same medication regimes will be administered for both conditions throughout the study. Pharmacotherapy falls under the responsibility of a psychiatrist and is provided independently of the current study.

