# Investigational product/treatment

The software platform serving the blended treatment (Minddisstrict) is not a medical device, based on the 2007/47/EG guideline of the European Parliament, The Wet Medische Hulpmiddelen (Law Medical Aids) (Date of validity 15-09-2013) and the flow chart which was developed by the Nictiz, based on the MEDDEV documentation for medical aids^[[1]](#footnote-1)^. The online part of the intervention can be seen as a digital self-help workbook. The website functions as well a secure environment in which the therapist and the patient can communicate through encoded transmission channels (https).

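### Adverse events are collected passively while face-to-face contact differs by arm, so any between-arm comparison of AE counts may be biased, probably towards fewer non-serious events in bCBT

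*Protocol*

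**What the plan says.** Protocol section 9.2.1 states the collection rule: "All adverse events reported spontaneously by the subject or observed by the" investigator or staff are recorded. Table 1 lists no AE item at any time point, and section 8.3 (Study procedures) schedules no AE enquiry.

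Face-to-face contact differs by design. In the blended arm "patients receive 6-10 face-to-face sessions and 6-10 internet sessions, which will be delivered over a period of 12-20 weeks" (section 5). For the comparator the Summary says "Treatment as usual will consist of 12 to 20 face-to-face CBT sessions on average", while section 5 says "patients receive on average 20 45-minutes sessions of face-to-face CBT".

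The blended arm also has remote contact. The therapist "provides weekly feedback prior to the next face-to-face session", and on the platform "the therapist and the patient can communicate through encoded transmission channels" (section 5.1).

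On risk, the Summary states: "Blended treatment is not considered to add risks to the treatment, compared to treatment as usual". Section 11 repeats this view. Section 10 contains no analysis of AEs.

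**The concern.** Under passive collection, an event enters the record only if someone has occasion to mention or notice it. During treatment, a therapy session is an obvious occasion, and the randomised treatment fixes how many face-to-face sessions there are. If bCBT then shows equal or fewer AEs, the reader cannot separate fewer events from less observation.

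The likely direction agrees with what the protocol assumes beforehand, that bCBT adds no risk. The trial also means to tell stakeholders whether blended treatment is advisable, and AE counts could be cited for that purpose. This has to be settled in the protocol, because analysis cannot restore events that were never elicited.

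**Working it through.** The protocol gives no AE rate, capture probability or safety power, so it has no figure of its own to reproduce on this point. The check compares planned contacts and then asks how much they could matter.

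**Step 1. Contact ratios (bCBT to CBT-TAU)**
- Face-to-face, Summary figures: 6/12 = 10/20 = 0.50.
- Face-to-face, against the average of 20 in section 5: 6/20 = 0.30 to 10/20 = 0.50. The 0.30 sets the short end of one arm's range against the other arm's average, so it is not like for like.
- All sessions, Internet sessions included, Summary figures: 12/12 = 20/20 = 1.0.
- All sessions, worst pairing with section 5: 12/20 = 0.60.

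**Step 2. Relative capture if only face-to-face sessions reveal events**

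Assume equal true event rates and the same probability q that an event comes to light at each of k sessions. Capture is 1 - (1 - q)^k. With twice as many sessions in CBT-TAU, the ratio is

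[1 - (1 - q)^k] / [1 - (1 - q)^(2k)] = 1 / [1 + (1 - q)^k],

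which always lies between 0.5 and 1. The document does not give q, so a range is shown:

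| q per session (assumed) | 6 vs 12 sessions | 10 vs 20 sessions |
| --- | --- | --- |
| 1% | 0.52 | 0.53 |
| 5% | 0.58 | 0.63 |
| 10% | 0.65 | 0.74 |
| 20% | 0.79 | 0.90 |
| 30% | 0.89 | 0.97 |
| 50% | 0.98 | 1.00 |

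At q = 10%, for example, capture is 1 - 0.9^6 = 0.469 against 1 - 0.9^12 = 0.718, a ratio of 0.65.

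**Step 3. Allowing for online contact**

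If an Internet session reveals events as well as a face-to-face session does, the ratio is 1.0 at any q. If it is half as good (5% against 10%), capture in bCBT is 1 - 0.9^6 × 0.95^6 = 0.609 with 6 + 6 sessions, a ratio of 0.609/0.718 = 0.85. With 10 + 10 sessions it is 1 - 0.9^10 × 0.95^10 = 0.791, a ratio of 0.791/0.878 = 0.90. If written contact prompts more reporting than a session does, the ratio exceeds 1.

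**Step 4. What this could look like in counts**

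Take 78 patients per arm (section 3), an assumed true risk of 20% in both arms and assumed capture of 80% in CBT-TAU. Then 78 × 0.20 × 0.80 = 12.5 patients with a recorded AE are expected in CBT-TAU. In bCBT the expectation is 12.5 if relative capture is 1.0, 9.4 if it is 0.75 and 6.2 if it is 0.5.

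**Step 5. Period affected**

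The contact difference applies to the 12-20 treatment weeks. The remaining 52 weeks to T3 have no protocol-scheduled sessions in either arm. They make up 52/72 = 72% to 52/64 = 81% of the observation time.

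**The case against.** A reader might infer that AEs will be under-counted in the blended arm and that it will look falsely safe. The documents do not support that, for five reasons.

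- **No AE comparison is planned.** AEs are not an endpoint, section 10 does not analyse them, and the no-added-risk statement is made in advance rather than drawn from counts. This stands. The harm is conditional on someone comparing or citing the counts.
- **The therapy session is not named as the reporting channel.** Section 9.2.1 refers to the investigator and staff in general. In bCBT, patients record feelings and behaviour online, the therapist follows this and gives weekly feedback, and messages can be exchanged. This stands in part. The direction is likely but not established, although the protocol does not make the platform a source of AE records.
- **Some harm-related data are already symmetric.** The TiC-P covers care use and absence. The BAI, BDI and BSI show worsening. Signs of relapse or suicidal ideation on study measures lead to contact with the therapist in both arms (section 8.3). This also stands in part, because none of these is said to generate an AE record.
- **Serious events take another route.** Centres notify possible SAEs within 24 hours in both arms (section 9.2.2). This stands, and it limits the concern mainly to non-serious events.
- **The ratios rest on assumed inputs.** This stands. They bound the problem under a simple model and do not estimate it.

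**Conclusion.** The concern holds in a limited form. AE ascertainment is passive, no common enquiry is scheduled, and face-to-face contact during treatment is about half as frequent in bCBT on the Summary's figures. Any between-arm AE comparison, or use of AE counts to support the absence of added risk, may therefore be biased, probably towards fewer non-serious AEs in bCBT.

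The size is unknown. With the Summary's session numbers it runs from near zero to about a halving of recorded events. It depends on capture per contact and on how far online feedback and messaging make up for lost meetings, and the protocol gives neither. SAEs are less exposed, and most of the follow-up period has no planned contact difference. No planned analysis is invalidated. This is a worthwhile, low-cost improvement.

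**What to change.** In section 9.2.1 and Table 1:

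- Add the same short AE question set, covering the time since the previous assessment, to the existing online questionnaires at T1, T2 and T3 in both arms. Scheduled enquiries are then 3 against 3, whatever the session count.
- State whether the relapse and suicidal-ideation alerts in section 8.3 are recorded as AEs.
- Record the source of each AE (session, platform, questionnaire or centre).
- Base any between-arm AE statement on the solicited data, and list spontaneous reports separately.

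Separately, the Summary and section 5 give different session counts for CBT-TAU and must be reconciled.

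The cost is a few items on a questionnaire that already takes 30 to 45 minutes, more AEs to record and one descriptive table. The sample size does not change. Two limits remain. Recall will be weak over the 52 weeks between T2 and T3. Patients also know their allocation (section 8.2), so common questions equalise the opportunity to report but not expectations.
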